### Sample size

2.7

It was absent of direct evidences to support t our hypothesis, consequently, estimating the sample size is difficult. At an 8-week study, the response rate of quetiapine in BD patients was 58.9%, and the remission rate was 42.1%.^[28]^ Combination therapy has been shown to be more effective. We estimated the effective rate of SFN combined with quetiapine in the treatment of bipolar depressive disorder to be about 70%. The sample size with 80% power at a significance level of 0.05 was calculated in this study. Anticipating a 10% dropout rate, a total of 100 patients, with 50 patients in each group, will be needed.

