### Outcomes

2.5

Primary outcome is the change in the MADRS scores at baseline compared to each treatment time point. MADRS is a clinician-administered rating scale and widely used to assess the depression severity of patient with BD. The response was defined as at least a 50% reduction when compared to baseline in the scores.

While secondary outcomes include the scores of the quick inventory of depressive symptomatology-self report, Hamilton anxiety rating scale, and YMRS scores are used to elevate the broader affective symptoms. Besides, cognitive function which tested by THINC-integrated tool, inflammatory factors (interleukin-2, interleukin-4, interleukin-6, interleukin-10, interleukin-17A, tumor necrosis factor and interferon-γ) and intestinal flora are used to investigate the underlying biological factors.

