### Statistical analysis

2.8

All statistical analyses will be performed using SPSS 19.0 software (IBM, Armonk, NY) in a blinded manner. Outcomes will be analyzed on the basis of intention-to-treat principle. Missing values will be handled by the practical guide described by Jakobsen et al. The comparison of primary outcomes and secondary outcomes between 2 groups will be performed by *t* test for continuous variables and *χ*^2^ test for categorical variables, or with Wilcoxon Mann–Whitney test. The paired *t* test will be used for analysis in each group. *P* < .05 will be considered significant

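### The 80% power stated for 50 per group cannot be reproduced from the response rates in section 2.7 (they give about 20%), and no power is given for the primary MADRS change

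*Protocol article*

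**What the plan says.** Section 2.7 (Sample size) opens by admitting that direct evidence is lacking and that sizing is difficult. It then cites an 8-week study in which "the response rate of quetiapine in BD patients was 58.9%, and the remission rate was 42.1" per cent. For the experimental arm it states: "We estimated the effective rate of SFN combined with quetiapine in the treatment of bipolar depressive disorder to be about 70" per cent. It goes on: "The sample size with 80% power at a significance level of 0.05 was calculated in this study". With 10% dropout the result is 100 patients, 50 in each group. The section gives no formula and no sidedness. It does not say which of the two control rates entered the calculation, or whether the 70% is a response or a remission rate.

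Section 2.5 (Outcomes) says: "Primary outcome is the change in the MADRS scores at baseline compared to each treatment time point". It defines response as a reduction of at least 50% from baseline and defines no remission outcome. Section 2.8 (Statistical analysis) compares groups by t test for continuous and chi-square test for categorical variables, or by the Wilcoxon Mann-Whitney test, under the intention-to-treat principle.

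**The concern.** A gain from 58.9% to 70% is 11 percentage points in the middle of the probability scale. Fifty patients per arm is far too few to detect that with 80% power, so either the stated power or the stated comparison must be something other than it appears.

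There is also a mismatch of endpoint. The calculation is in terms of a proportion, but the primary outcome is a change in score that would be compared by t test. Power for one does not carry over to the other, and the protocol supplies no MADRS difference or SD from which to derive it.

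The stake is how a null result will be read. A reader who trusts the 80% will take a non-significant comparison as fair evidence that SFN adds nothing. If the assumed response gain were real, the response comparison would miss it about four times in five.

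**Working it through.** **Inputs.** From section 2.7: control response 0.589, control remission 0.421, experimental rate 0.70, power 80%, significance level 0.05, dropout 10%, 50 per group. Allocation is 1:1 (section 2.1). Sidedness is not stated, so both are shown. The evaluable number after dropout is 50 × 0.90 = 45 per arm.

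**Step 1: reproduce 45 (or 50) per arm from the response rates.** The pooled two-proportion formula is n = [z(α)·A + z(β)·B]² / d², with A = √(2·p̄·(1 − p̄)) and B = √(p₁(1 − p₁) + p₂(1 − p₂)).

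- p̄ = (0.589 + 0.70)/2 = 0.6445, and d = 0.111
- A = √(2 × 0.6445 × 0.3555) = 0.6769
- B = √(0.2421 + 0.2100) = 0.6724
- n = (1.960 × 0.6769 + 0.8416 × 0.6724)² / 0.111² = 1.8926² / 0.012321 = 290.7, so 291 per arm
- Unpooled: n = (1.960 + 0.8416)² × 0.4521 / 0.012321 = 288 per arm

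| Variant, 58.9% vs 70% | Evaluable per arm, two-sided | Evaluable per arm, one-sided |
|---|---|---|
| Pooled | 291 | 229 |
| Unpooled | 288 | 227 |
| Arcsine | 291 | 229 |
| Pooled, continuity-corrected | 309 | 247 |

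The two-sided pooled figure becomes 291/0.90 = 323.3, so 324 per arm after dropout. No variant comes near 45 or 50; 291/45 is more than sixfold.

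**Step 2: power at the planned size.** Power = Φ[(d√n − z(α)·A)/B].

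- n = 50: (0.111 × 7.071 − 1.3268)/0.6724 = −0.806, so power is 21.0% (exact enumeration of the uncorrected chi-square test: 21.1%)
- n = 45: (0.111 × 6.708 − 1.3268)/0.6724 = −0.866, so power is 19.3% (exact: 20.1%)
- One-sided: 31.3% at 50 and 29.2% at 45

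Against 58.9%, 80% power (two-sided) needs about 84% response at 50 per arm or 85% at 45, a gain of 25 to 26 points instead of 11. At the assumed rates the 95% interval for the difference has half-width 1.96 × √(0.4521/n), which is 19 points at n = 50 and 20 at n = 45.

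**Step 3: try the other control rate in the section.** For 42.1% against 70%, d = 0.279, A = 0.7019 and B = 0.6736.

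- Two-sided, pooled: (1.960 × 0.7019 + 0.8416 × 0.6736)² / 0.279² = 48.5, so 49 per arm; unpooled 46 per arm
- Two-sided power: (0.279 × 7.071 − 1.3757)/0.6736 = 0.886, so 81.2% at 50; 76.9% at 45
- After dropout: 49/0.90 = 54.4 and 46/0.90 = 51.1, so slightly above 50
- A one-sided, continuity-corrected calculation gives 45 evaluable, and 45/0.90 = 50 exactly

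The stated size is therefore roughly recovered with the remission rate as comparator, and exactly recovered in one unusual variant.

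**Step 4: the primary outcome.** For a two-sample t test at 0.05 two-sided, 80% power is reached at a standardised difference of 0.597 with 45 per arm and 0.566 with 50. The normal approximation (1.960 + 0.8416) × √(2/n) gives 0.591 and 0.560. The protocol states no MADRS difference or SD to set beside these.

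As an illustration only, assume that response is a cut on a normal scale with equal SDs. The assumed shift is then probit(0.70) − probit(0.589) = 0.30 SD, for which the t test has 29% power at 45 and 32% at 50. That mapping is an assumption, not a figure from the protocol.

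**The case against.** The best defence is that section 2.7 never says 58.9% was the comparator and calls the 70% an effective rate, not a response rate. If the 70% was meant as remission, 42.1% against 70% gives 77 to 81% power and the statement roughly holds. This stands to the extent that a reader might infer that the 80% is simply false, and the text does not support going that far. It does not rescue the section: the protocol defines response and no remission outcome, and nothing in it says that the 70% is a remission rate.

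A reader might also infer that a remission rate was compared with a response rate by mistake. That is only a guess. The text contains no such comparison, and the reconstruction fits 50 per group exactly only with a one-sided, continuity-corrected test.

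A further temptation is to object that the rates come from an 8-week study while the trial lasts 12 weeks. That does not hold. Assessments fall at weeks 2, 4, 8 and 12, and the primary outcome covers each treatment time point, so week 8 is among them.

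Nor does the figure of about 20% apply to the primary analysis. It belongs to the response comparison; power for MADRS change is unknown on what the protocol states.

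Finally, section 2.7 concedes the lack of evidence, and the Discussion calls the trial exploratory and asks for cautious interpretation. This lowers the risk of over-reading a null result, but it leaves the power sentence uncorrected.

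**Conclusion.** The concern holds in limited form. The stated 80% power does not follow from the response rates given: 45 to 50 per arm give 19 to 21% two-sided (29 to 31% one-sided), and 80% would need 288 to 291 evaluable per arm (two-sided). About 80% appears only with the remission rate as control, on a reading of the 70% that the protocol does not state. Separately, the sizing concerns a proportion while the primary outcome is a score change, so no stated input supports any power for the primary analysis.

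The response figures assume that the 70% means response as section 2.5 defines it and that the test is at level 0.05. They hold under every standard formula tried. The detectable difference of 0.57 to 0.60 SD assumes a two-sided t test at a single visit. As written, the sentence needs correcting.

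**What to change.** Keep 100 patients and replace the power sentence in section 2.7. The new text should:

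- name the endpoint and the control rate that the calculation used, and say whether the 70% is response or remission;
- state that for 58.9% against 70% response, the planned size has about 20% power (two-sided 0.05);
- state that for a t test on MADRS change at any single visit, 45 to 50 evaluable per arm give 80% power for a standardised difference of about 0.60 to 0.57;
- say that results will be reported as estimates with 95% confidence intervals, in line with the exploratory label in the Discussion, so that a null result is not read as no effect.

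If the 0.30 SD conversion and its 29 to 32% power are mentioned at all, they should be labelled as an assumption.

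The cost is a rewording by amendment, with no extra patients and no change in conduct. The price is that the stated power becomes much less favourable.

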### Statistical analysis

2.8

All statistical analyses will be performed using SPSS 19.0 software (IBM, Armonk, NY) in a blinded manner. Outcomes will be analyzed on the basis of intention-to-treat principle. Missing values will be handled by the practical guide described by Jakobsen et al. The comparison of primary outcomes and secondary outcomes between 2 groups will be performed by *t* test for continuous variables and *χ*^2^ test for categorical variables, or with Wilcoxon Mann–Whitney test. The paired *t* test will be used for analysis in each group. *P* < .05 will be considered significant

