### Study design and ethics approval

2.1

This is a randomized, double-blinded, placebo-controlled, parallel-group clinical trial. This protocol was approved by the Research Ethics Committee of the First Affiliated Hospital, College of Medicine, Zhejiang University (December 24th, 2019). The trial which is registered at the Chinese Clinical Registry (ChiCTR2000028706) will be conducted in the First Affiliated Hospital, College of Medicine, Zhejiang University in China. The clinic trial was supported by the grant of the National Natural Science Foundation of China (81971271). Figure 1 depicts a flow chart of the study. Patients enrolled in this study will randomly be assigned into 2 groups (with a 1:1 allocation ratio). Clinical manifestations and assessment scales, neurocognitive functions, and some of the blood biochemical tests will be checked before treatments started (baseline) and will be reexamined on week 2, 4, 8, 12 weeks of treatment to assess the effectiveness and safety. Meanwhile, inflammatory cytokines and intestinal flora were monitored during follow-up. Researchers will record and deal with the any adverse reactions and assess whether they can continue the experiment to protect the participants’ interests during the study. Specific schedules are summarized in Table 1.

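### MADRS change is compared between arms without baseline MADRS as a covariate, which is valid but generally less precise than an adjusted analysis of the same data

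*Protocol article*

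**What the plan says.** Section 2.5 (Outcomes) defines the endpoint: "Primary outcome is the change in the MADRS scores at baseline compared to each treatment time point". It also defines response: "The response was defined as at least a 50% reduction when compared to baseline in the scores".

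Section 2.8 (Statistical analysis) then fixes the method: "The comparison of primary outcomes and secondary outcomes between 2 groups will be performed by" a t test for continuous variables and a chi-square test for categorical ones, "or with Wilcoxon Mann–Whitney test". The only other analysis named is within arms: a paired t "test will be used for analysis in each group". Section 2.8 mentions no covariate, analysis of covariance or longitudinal model.

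Section 2.1 (Study design and ethics approval) shows that the data for an adjusted analysis will exist. The assessment scales "will be checked before treatments started (baseline) and will be reexamined on week 2, 4, 8, 12 weeks of treatment".

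**The concern.** The between-arm method is stated, so this is a choice that can be assessed and not a detail left to an unseen analysis plan. For MADRS change it is an unadjusted two-sample comparison, repeated at each visit. The paired test within each arm does not compare the arms and cannot stand in for adjustment.

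Subtracting baseline is the same as assuming that follow-up MADRS rises by exactly one point for each baseline point. If the true slope differs from 1, two things follow:

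- The treatment estimate has a larger standard error than it needs.
- Given a chance baseline difference between arms, the estimate is moved by part of that difference. Section 2.3 describes 1:1 randomisation and mentions no stratification by severity.

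At stake is precision in a trial of 50 per arm, which has little to spare. In addition, the text as written settles neither which of the two tests nor which visit supplies the primary result.

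**Working it through.** **The plan's own figure.** Section 2.7 gives 100 patients for 80% power at 0.05 with 10% dropout. It cites that "the response rate of quetiapine in BD patients was 58.9%, and the remission rate was 42.1"%, and adds: "We estimated the effective rate of SFN combined with quetiapine in the treatment of bipolar depressive disorder to be about 70"%. For 58.9% against 70%, two-sided:

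n per arm = [1.960·√(2·0.6445·0.3555) + 0.842·√(0.589·0.411 + 0.70·0.30)]² / 0.111² ≈ 291

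Allowing for dropout, 291/0.9 gives 324 per arm, or 648 in total. One-sided, the total is 510. Neither is 100. Two-sided power for this contrast is about 21% with 50 per arm and 19% with 45. This matters here only as evidence that precision is scarce. The sample size rests on a response rate, not on MADRS change, so covariate adjustment does not correct it.

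**Inputs for the adjustment question.**

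- Arm size: 50, or 45 evaluable after the 10% dropout (section 2.7).
- MADRS SDs at baseline (SD_b) and follow-up (SD_f), and their correlation r: not given in the article. I assume r from 0.3 to 0.7 and q = SD_b/SD_f of 0.6, 0.7, 0.8 and 1.

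**Formulas**, per patient at a single visit, in units of SD_f²:

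- Change score: 1 + q² − 2rq
- Baseline-adjusted: 1 − r²
- Ratio R = (1 − r²)/(1 + q² − 2rq), which is (1 + r)/2 when q = 1

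| q | r = 0.3 | r = 0.5 | r = 0.7 |
|---|---|---|---|
| 1.0 | 0.65 | 0.75 | 0.85 |
| 0.8 | 0.784 | 0.893 | 0.981 |
| 0.7 | 0.850 | 0.949 | 1.000 |
| 0.6 | 0.910 | 0.987 | 0.981 |

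Examples: for q = 0.8 and r = 0.3, 0.91/1.16 = 0.784. For q = r = 0.7, 0.51/0.51 = 1. R reaches 1 only when r = q, that is, when the slope r/q equals 1.

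**In patients.** With equal SDs, 90 evaluable patients under adjustment are worth 90/R under the planned test: about 138, 120 and 106 at r = 0.3, 0.5 and 0.7. In the least favourable rows the equivalent falls to 90, which is no gain.

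**In power.** Where the planned test has 80% power, effect/SE = 1.960 + 0.842 = 2.802. Adjusted power is then Φ(2.802/√R − 1.960), by normal approximation.

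- Equal SDs: 93.5%, 89.9% and 86.0% at r = 0.3, 0.5 and 0.7.
- q = 0.6 to 0.8: from 80% (R = 1) to 89% (R = 0.784).

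**Chance imbalance.** With 50 per arm, the standard error of the baseline difference is SD_b·√(2/50) = 0.2 SD_b. A baseline difference D moves the expected change-score difference by (slope − 1)·D, where slope = r/q.

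- q = 1, r = 0.5: a one-standard-error imbalance moves it by 0.5 × 0.2 = 0.10 SD, against the direction of the imbalance.
- q = r = 0.7: slope 1, no shift.
- q = 0.6, r = 0.7: slope 0.7/0.6 = 1.17, so the change score under-corrects.

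**The case against.** Much of the case on the other side is sound.

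- **Baseline and visits are used.** A reader might infer that the plan ignores baseline MADRS and the repeated visits. It does not. The change score subtracts baseline, and every visit is compared. What is absent is baseline as a covariate and a joint model of the visits.
- **The test is valid.** A reader might infer that the primary result will be biased. Over repeated randomisations the t test on change is unbiased with correct type I error. Only the estimate given an observed imbalance shifts.
- **Over-correction is not universal.** It requires r below SD_b/SD_f. A correlation below 1 is not enough.
- **The gain may be nil.** Section 2.2 requires a Hamilton depression score of at least 17 and excludes patients scoring 3 or more on MADRS item 10. This could narrow the baseline spread, which is where the gain shrinks. Quoting only the equal-SD figures would overstate the benefit.
- **Test selection.** A reader might infer that the P value will be picked after the data are seen. Section 2.8 says the analyses are done blinded, and the rule for switching to Mann-Whitney may stand in an analysis plan not shown. The article supports only the statement that it gives no such rule.
- **Exploratory status.** The Discussion calls the trial exploratory. That lowers the stakes, but section 2.7 still claims 80% power and section 2.8 still applies P < .05.

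What survives is that, apart from one degree of freedom, the adjusted analysis is not less precise anywhere in the range, and it uses data already scheduled.

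**Conclusion.** The point holds as one of efficiency and specification, not of validity. The unadjusted comparison is generally less precise than a baseline-adjusted one, and it leaves the estimate exposed to chance baseline imbalance unless the slope of follow-up on baseline is 1.

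Overall, the variance saving lies between nil and about 35%. The range rests on assumed correlations of 0.3 to 0.7 and SD ratios of 0.6 to 1, because the article gives neither quantity. It refers to adjustment at a single visit; any further gain from modelling the visits jointly is not quantified here.

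A reader might also infer that adjustment would make 100 patients enough. The article does not support that, since its sample size is built on response rates.

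**What to change.** In section 2.8, replace the between-arm t test for MADRS with one named model:

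- a linear model of MADRS change on arm, with baseline MADRS as covariate; or
- a mixed model for repeated measures over weeks 2, 4, 8 and 12, with arm, visit, arm-by-visit and baseline terms.

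State that the primary contrast is read at one visit, named by the sponsor in advance. Week 12, the end of treatment, is an example; the article designates no visit. Use the same form for the continuous secondary scales, and keep Mann-Whitney as a named sensitivity analysis.

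The cost is a change of wording before unblinding, one degree of freedom and slightly more analysis work. Both models are routine in SPSS, and no new data or visits are needed. The sample-size calculation in section 2.7 needs separate attention.

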## Discussion

3

As a chronic and complex mood disorder, the treatment of BD frequently required combinations of therapies. A number of pharmacotherapeutic treatments with side effects induce low adherence of patient and poor outcomes. Nutraceutical agents with higher acceptability are more and more considered to improve treatment for the symptoms of BD as adjunctive therapies.^[29]^ In the treating mental disorders, SFN has been proved have a significant improvement in mood and cognitive function by regulating peroxidation reactions.^[25,30]^ The aim of this randomized clinical trial is to investigate the effect of SFN as an adjuvant role in the treatment of bipolar depressive disorder.

In this study, besides using the MADRS, Hamilton depression scale, Hamilton anxiety rating scale, quick inventory of depressive symptomatology-self report, and YMRS scales to assess the clinical curative effect on emotional problem, THINC-integrated tool will be introduced to evaluate neurological status. In addition, we monitor inflammatory factors including serum concentration of and intestinal flora before and after treatment to explore the possible mechanism of SFN combined with quetiapine on treating bipolar depressive disorder. In summary, we expected that our findings will provide evidence for efficacy and safety of SFN as an adjuvant treatment of BD.

This study also has some limitations. First, this is an exploratory trial with evaluating the intervention by various outcomes and process measures from multiple perspectives, the results should be cautiously interpreted. Besides, as a nutritional supplement, the dose of SFN in the preliminary study is conventional, but perhaps that's not necessarily a most effective dose. Thus, further study is required to explore an optimal dose plan for SFN as an adjuvant in the treatment of bipolar depressive disorder.

In summary, this trial is expected to provide initial findings on the synergistic effect of SFN in the treatment of BD. If, as expected, combination of quetiapine and SFN therapy could have more positive effects, it will provide an opportunity to increase the availability of evidence treatment for patients with BD.
